### Data handling and record keeping

All demographic data will be recorded by Tanzanian fieldworkers using Android smartphones containing pre-programmed, pre-tested, standardized data entry forms which will be uploaded directly to an electronic server. Each LN will have a unique ID number and study subjects participating in the cross-sectional surveys will be identified by their demographic enumeration number. All forms and datasets will record participant data using these codes; no personal identifiers will be entered.

All data computers will be password protected with restricted access to only authorized study investigators and data management staff; field workers will have no access to the server. Only the PI and senior field investigators will have access to the full master LN list. A copy of the master list without household identifiers will be submitted to WHOPES. Laboratory data will be recorded on standardized forms and double-entered, firstly by field workers and then by dedicated data entry staff, and the entries combined and errors corrected to produce a single dataset. Daily data checks will be performed to identify incomplete, missing, inaccurate or inconsistent data. Datasets will be checked for consistencies by generic and study specific algorithms designed to identify sources of error. When inconsistencies arise, these will be compared to the original forms and subsequently rectified by the appropriate study investigator.

Demographic and entomological data will be kept separately from that containing personal information. Data will be stored for at least 10 years as per standard NIMR practice. The PI will maintain appropriate medical and research records in compliance with good clinical practice (GCP) and regulatory and institutional requirements. Authorized representatives of the sponsor, the ethics committee(s) or other regulatory bodies may inspect all documents and records at any time. The PI will ensure access to facilities and records, as required.

### Data analysis

All statistical analyses will be performed using STATA version 13 (StataCorp LP, College Station, TX, USA).

Bioefficacy data from the WHO cone tests will be used to calculate proportional knock-down and mortality. Bioefficacy results from the netting pieces of each LN will be pooled to determine whether the net meets the WHO efficacy criteria of ≥80% mortality or ≥95% knockdown. Bioefficacy data from the WHO tunnel tests will be used to determine whether nets that fail the cone test meet the WHO efficacy criteria of ≥80% mortality or ≥90% blood-feeding inhibition. Blood-feeding inhibition will be assessed by comparing the proportion of blood fed females (alive or dead) in treated and control tunnels. Overall mortality will be measured by pooling the immediate and delayed (24 h) mortalities of mosquitoes from the two sections of the tunnel, relative to the control. Mortality data in both WHO cone and tunnel tests will be corrected for negative control mortality using Abbott’s formula.

A candidate LN product must achieve the WHO requirement of at least 80% of sample nets meeting the bioefficacy criteria in the WHO cone bioassays or tunnel tests after 3 years of use.

Chemical analysis results will measure the mean (and standard deviation) target deltamethrin concentration in each type of LN to assist interpretation of the bioefficacy data. Insecticide content reported at each survey time will be used to estimate the average rate of insecticide loss from the original loading dose.

LN survivorship will be measured at each timepoint as the total number of each LN present in surveyed households (and used for sleeping under) divided by the total number of each LN originally distributed to households and not given away at each time point [6]. Median LN survival is the time point at which the estimate of functional LN survival reaches 50%. LN attrition is derived from the total number of LNs missing from each household (classified into categories of nets that have been destroyed or disposed for reasons other than poor fabric integrity, nets used for other purposes and nets destroyed for reasons of poor fabric integrity) divided by the total number of each LN distributed to households. LNs retained for inspection but no longer used for reasons of poor integrity will be included among the nets lost to attrition.

Fabric integrity during the field trial will be assessed using various criteria: 1) the proportion of LNs with holes (total number of each LN product with at least one hole of any size, divided by the total number of each LN product surveyed); 2) the proportional hole index (calculated by weighting each hole by size and summing for each net (Table 3) [28]; and 3) hole area and circumference. For each LN product, fabric integrity indices will be compared by analysis of variance for normally distributed data or the Kruskal-Wallis test or Poisson regression for non-parametric data.

Multivariate regression analysis will be used to identify factors that influence LN durability and community acceptability of each net product, using variables derived from household questionnaire data.

Fabric strength and resistance-to-damage tests [37] will be based on bursting strength and wounded bursting strength (EN ISO 13938-2, a measure of tear resistance), hook tensile strength (ISO 13934-2), snag strength (adapted EN 15598), abrasion resistance (ISO 12947:1998) and hole propagation tests (multi axial loading of wounded bursting strength test) of LNs collected from the field and will be correlated with LN durability indices.

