### Cross-sectional surveys: fabric integrity

At t6, 12 and 18 months post LN distribution, the 30 LNs destructively sampled for bioassays will be scored for physical integrity by draping the nets over a frame and counting the number and types (due to burning, tearing, split seams or animal damage) of holes of different sizes according to location on the net (top, upper side, lower side). Holes greater than 0.5 cm will be classified into the following categories: smaller than a thumb (0.5–2 cm); larger than a thumb but smaller than a fist (2–10 cm); larger than a fist but smaller than a head (10–25 cm) and larger than a head (>25 cm). At t24 and 36, physical integrity of the nets will be evaluated for a randomly selected sample of 100 LNs of each brand (including the 30 destructively sampled for bioassays). Net integrity (hole index, hole area and circumference) of each net type will be calculated as per WHO guidelines [28] (Table 3). In addition, any evidence of repairs and types of modification will be recorded.

**Table 3 Tab3:** LN hole size index

Hole Size Categories (cm)	Hole Diameter^a^ (*d;* cm)	Hole radius (*r* = *d/*2)	Hole Area^b^ (π**r* ^2^)	Hole Index^c^
0.5–2.0	1.25	0.625	1.23	1
2–10	6	3	28.28	23
10–25	17.5	8.75	240.56	196
>25	30	15	706.95	576

^a^Weights for each size category were estimated assuming that the average hole diameter was the midpoint in each category, except for the largest hole where the average diameter was assumed to be 30 cm

^b^The approximate area of an average sized hole from each category was estimated by assuming each hole was approximately circular

^c^Final weights for each size category were then estimated by dividing the area encompassed by a hole in the smallest size category (i.e. 1.23)

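### Poisson regression is offered as a method for non-parametric fabric integrity data, yet none of the listed indices is a Poisson count; with model-based errors it would often separate identical nets

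*Protocol article*

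**What the plan says.** The Data analysis section of the Protocol article lists three sets of fabric integrity criteria: "the proportion of LNs with holes"; a hole index, "calculated by weighting each hole by size and summing for each net"; and "hole area and circumference". The number of holes is recorded in the field, but it is not on this list as an index of its own.

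One sentence covers the comparison of products on all of them: "fabric integrity indices will be compared by analysis of variance for normally distributed data or the Kruskal-Wallis test or Poisson regression for non-parametric data". It does not tie Poisson regression to a particular index, gives no rule for choosing between it and Kruskal-Wallis, and names no variance estimator.

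Table 3, under Cross-sectional surveys: fabric integrity, fixes the index weights at 1, 23, 196 and 576. Its footnote explains: "Final weights for each size category were then estimated by dividing the area encompassed by a hole in the smallest size category".

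**The concern.** The label is wrong: Poisson regression is fully parametric and is no remedy for data that fail a normality check. The model also fits none of the listed outcomes. Under the Table 3 weights, one hole over 25 cm adds 576 to a net's index, and a Poisson likelihood reads that as 576 independent events. Model-based standard errors would then be too small.

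The Discussion says the trial is designed primarily to compare the field durability of three polymers, and fabric integrity is part of durability in the stated objectives. Overstated significance on the hole index would bear directly on that comparison. Two permitted tests that can disagree sharply on the same data also leave room for choosing after the results are seen.

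**Working it through.** **Reproducing Table 3.** The weight is (d/1.25)² for the assumed hole diameter d in cm.
- d = 1.25: 1
- d = 6: 4.8² = 23.04, printed as 23
- d = 17.5: 14² = 196
- d = 30: 24² = 576

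The printed areas follow with π = 3.142, for example 3.142 × 15² = 706.95. The table is internally sound.

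**Variance/mean of the index.** The article gives no mean, SD or distribution of holes, so the hole counts below are assumptions. If holes in each size class are independent Poisson with means λ, then

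φ = Σw²λ / Σwλ.

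Poisson regression assumes φ = 1, so its model-based standard errors are too small by a factor √φ. With three identical products the 2-df statistic behaves as φ times a chi-square on 2 df. The rejection rate at nominal 5% is therefore

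exp(−5.99/(2φ)).

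| Assumed mean holes per net (0.5–2, 2–10, 10–25, >25 cm) | φ | √φ | Three-arm rejection |
|---|---|---|---|
| 60 small per 1 medium, none larger (only the ratio matters) | (60 + 529)/(60 + 23) = 7.1 | 2.7 | 66% |
| 3, 1, 0, 0 | (3 + 529)/(3 + 23) = 20.5 | 4.5 | 86% |
| 1, 0.5, 0.1, 0.02 | 10,742.62/43.62 = 246 | 15.7 | 99% |
| 4, 2, 0.5, 0.15 | 70,036.4/234.4 = 299 | 17.3 | 99% |

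Simulation of identical products agreed: about 65%, 85–86% and 99%. The excess does not shrink with sample size. It is the same at 30, 100 and 150 nets per arm, the sizes the article gives for the surveys to 18 months, the 24- and 36-month surveys, and the cohort.

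**Range.**
- If every hole is under 2 cm and nets do not differ in their hole rate, φ = 1 and the test holds 5%.
- Gamma variation between nets with shape k adds (mean index)/k to φ. In the second row the mean is 26, so k = 1 raises φ from 20.5 to 46.5.
- A two-arm comparison is less extreme: 2 × [1 − Φ(1.96/√φ)] gives 67% at φ = 20.5 and 90% at φ = 246.

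**Alternatives on simulated data from identical products, nets independent.** Kruskal-Wallis rejected about 4–6% of the time. Poisson regression with a sandwich variance rejected about 5–12%. The high end was at 30 nets per arm with rare large holes; at 150 per arm it was about 5–7%.

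**Hole area and its unit.** Area in cm² is about 1.23 times the index, so φ is about 1.23 times as large. Rescaling the outcome rescales φ. For the last row of the table:
- cm²: φ ≈ 1.23 × 299 = 368, rejection 99%
- dm²: φ ≈ 3.68, rejection exp(−2.996/3.68) = 44% (45% simulated)
- m²: φ ≈ 0.037, rejection essentially 0%

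The same nets give opposite conclusions depending on the unit recorded.

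**The case against.** Several points on the other side stand.

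- **Poisson is not prescribed.** It is one of two alternatives and is assigned to no index. Kruskal-Wallis, in the same sentence, avoids the inflation when nets are independent. A reader might infer that the plan must produce false differences; the text shows only that it permits a method that would.
- **No variance is documented.** A reader might take it as fact that the index's variance is hundreds of times its mean. That figure rests on assumed counts that include some holes over 10 cm. With lighter damage the ratio is much smaller, possibly so at early surveys.
- **The inflation needs model-based standard errors.** The article names no estimator, and a condensed article may leave that to an analysis plan that is not shown. A robust variance removes most of the inflation, and a robust Wald test does not change with the unit.
- **The order of products is not affected.** With arm as the only factor, the fitted means are the sample means whatever the overdispersion. A reader might infer that the ranking would be noise; the damage is to p-values and intervals.
- **The regulatory criterion is bioefficacy.** The Discussion notes that no fabric durability threshold has been set. But it also calls relative durability the primary design purpose, so the outcome still matters.

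None of this rescues the sentence itself. It mislabels a parametric count model, offers it for outcomes that are not counts, and gives no rule for avoiding it.

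**Conclusion.** The point holds as a fault in what the plan permits. Poisson regression is wrongly classed as a method for non-parametric data and suits none of the listed indices. If it were used with model-based standard errors on the hole index, a three-arm test of identical products would reject about 65% of the time with almost only small holes, about 85% with small and medium holes, and about 99% once some holes exceed 10 cm.

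These figures assume a 5% level, independent Poisson holes and independent nets; only the weights come from the article. Variation between nets would raise them. Damage confined to holes under 2 cm, with no such variation, would remove the excess. For hole area the direction of the error depends on the unit. The near-5% rate for Kruskal-Wallis likewise assumes independent nets.

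**What to change.** - **Hole index, area and circumference:** remove Poisson regression with model-based errors and name one method before the data are analysed. It can be Kruskal-Wallis, or a model of the mean or of log(index + 1) with robust variance. These answer different questions, so the choice should follow from whether mean damage or the general distribution of damage is the target. At 30 nets per arm a robust variance may still be somewhat liberal.
- **Unit of analysis:** the Study design section says all participating households in a hamlet receive one type of net, across eighteen hamlets. If the hamlet is the unit that received one net type, apply the chosen test to hamlet summaries or calculate the robust variance at hamlet level.
- **Number of holes, if analysed:** a count model that allows overdispersion.
- **Proportion of nets with holes:** a binary model.

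The cost is a change of analysis wording and software command. Fieldwork is unaffected, and the article's Trial status (monitoring year 2) leaves time before the final survey. The downside is that p-values and intervals will look less favourable than those from model-based Poisson regression with area in cm² or the index itself.

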## Discussion

A recent WHO consultation to review the evidence on the fabric strength of LNs concluded that the current data on the durability of LNs are inadequate, variable and poor quality, and that direct prospective trials to compare different brands of net in a variety of field settings are necessary [37]. To our knowledge the present proposed trial is the first to compare three types of LN polymer – polyester, polyethylene and polypropylene - in the same location using a prospective randomized controlled trial design.

WHOPES Phase III bioefficacy guidelines for LNs are currently based on retention of bioefficacy rather than physical durability. To obtain a WHOPES full recommendation at least 80% of the LNs surviving 3 years of household use in malaria endemic countries must retain sufficient insecticidal activity to induce 80% mosquito mortality in bioassay tests [28]. Four brands of LN have already achieved this criteria: polyester nets, PermaNet 2.0® and Interceptor® [35, 40], and polyethylene nets, Olyset® and DuraNet® [41, 42]. A further four LNs have obtained WHO full recommendations on the basis of equivalence to the aforementioned brands, and a further eight have obtained WHO interim recommendation after demonstrating bioefficacy in Phase II experimental hut trials [25]. While most brands of LN may achieve the requisite levels of bioefficacy, it is much less clear whether all types of net can physically withstand the wear and tear of 3 years of household use. LN survival will depend on the environment and household conditions of use. A LN stretched over a rustic wooden bed in a cramped traditional mud house will not last as long as a properly fitted LN draped over a bespoke net frame in a rodent free home. The duration of the mosquito season will also affect LN longevity and usage, and this will differ between the tropics and subtropics, highlands and lowlands, and coastal and plain areas [4, 15]. In practice, few brands of LN have undergone rigorous longitudinal monitoring. The first LNs to obtain WHOPES full recommendation - polyester PermaNet 2.0® LN and polyethylene Olyset® LN - were the subject of annual cross-sectional surveys of random samples of nets [35, 42] across a number of countries after 1–3 years of use rather than longitudinal monitoring of a documented cohorts of nets [28]. In these surveys it was noted that net integrity (hole index) reached a steady state after 2 years of use indicating that LNs with higher hole indexes were being discarded and not surviving to 3 years. In these countries only one brand of net had been distributed. Unless different types of LNs are tested in the same location, in parallel, in household randomized trials, it will be difficult to determine their relative durability under field conditions. Few LN brands have been evaluated against one another in this way. A recent exception was a household randomized trial in Cambodia between polyethylene Netprotect® LNs and polyester PermaNet 2.0® LNs [43]. Net survivorship exceeded 90% in the first 2 years but after 3 years decreased to ~60% for both LNs, indicating that nets of either material were unable to last much longer than 2 years. It is therefore appropriate that the proposed trial of a longer lasting polypropylene LN is assessed alongside and against polyester and polyethylene LNs over 3 years of field use.

A standard WHOPES phase III trial of a LN normally compares the candidate LN to a reference LN (positive control) made from the same material to determine insecticide bioefficacy after 3 years of field use [28]. While the proposed field trial uses the WHOPES phase III guidelines and may ultimately lead to a WHO recommendation for LifeNet® LN, it is primarily designed as a randomized controlled trial to compare the relative field durability of three types of LN polymer. Increasing the current average lifespan of LNs is a priority for the WHO. LNs with longer life cycles would need to be replaced less frequently, thus reducing the unit cost of LN distribution and replacement [6, 37]. A WHOPES evaluation criterion based on durability would also create a stimulus for manufacturers to improve performance of their products [6]. Based on current data, WHOPES has been unable to set a fabric durability threshold that a candidate LN should meet. The WHO Technical Expert Group on malaria vector control has proposed the setting of a median LN survival time based on functional LN survival at a given time after distribution. It is hoped that the present comparative study of polypropylene, polyester and polyethylene LNs would provide evidence to help calculate that criterion for different types of LN. Looking forward beyond current pyrethroid LNs to a future of nets treated with alternative insecticides to combat pyrethroid resistant mosquitoes, more durable fabrics may be necessary to maintain LN unit costs to a reasonable level [44, 45].

It is not clear whether the physical durability of LNs in the field can be anticipated by laboratory tests of fabric strength. The WHO consultation that recently reviewed the utility of fabric strength tests concluded that their usefulness for predicting LN durability in the field has yet to be determined, and recommended comparative prospective studies with various types of LN in a single study environment [37]. It is intended that the present study will match the indicators of field durability (hole index and functional survival) with those of laboratory strength tests to predict the durability of LNs in operational settings.

Experience has demonstrated that net attrition can be due to a variety of reasons other than loss of integrity. In the trial of Netprotect® and PermaNet 2.0® LNs in Cambodia, twice as many nets were lost or stolen, sold or given away, than were no longer used due to loss of integrity [43]. In the WHOPES funded evaluation of ICON® Maxx in Tanzania from 2011 to 2014, only 17% of nets survived 3 years of monitoring [46]. While 32% of nets failed due to loss of integrity, 52% were absent for other reasons, including families moving home, seasonal absences, selling or giving nets away. Such losses reduced power to detect an effect from the intervention, and should be discouraged provided the right to withdraw from the trial remains paramount. To encourage responsible net use, study participants/families were requested before recruitment to the cohort component of the trial not to give away or sell the study LNs. They were afforded the freedom to stop using the LNs at any time but to let investigators know the reasons during the next follow up survey. Study participants were informed that LNs would be replaced after 3 years (at the end of the trial period and not before) regardless of net condition but only on production of the trial net. If participants stopped using the LN for any reason, including accumulation of holes, they were to store the net for replacement, or give it to the investigators who would replace it after the trial period has elapsed. These revisions to Phase III guidelines were approved by the WHO and reported by the WHOPES working group in 2014 [46]. Such consent by participants would fulfil the needs of the trial and potentially reduce non-attrition losses, but would not affect participants’ right to stop using their net at any time with impunity.

### Trial status

Monitoring period year 2.

## Abbreviations

AE: Adverse event
AI: Active ingredient
CIPAC: Collaborative International Pesticides Analytical Council
DMO: District medical officer
GC: Gas chromatography
GCP: Good clinical practice
GFATM: Global Fund to Fight AIDS, Tuberculosis and Malaria
GPS: Global positioning system
ID: Identification code
IRS: Indoor residual spraying
LN: Long-lasting insecticidal net
LSHTM: London School of Hygiene and Tropical Medicine
MRCC: Medical research coordinating committee
NIMR: National Institute for Medical Research
NMCP: National Malaria Control Program
PI: Principal Investigator
UCC: Universal coverage campaign
WHO: World Health Organization
WHOPES: WHO Pesticide Evaluation Scheme
